#### Statistical analysis

2.1.11

Data will be kept anonymous and non-identifiable. For the statistical, analysis, R software^[30]^ and the Mplus computer program will be used.^[31]^ Data collection will include the most relevant demographic variables allowing us to compare collected data within a population. Reweighting and other techniques will allow adjustment for known or expected discrepancies between sample populations.^[32]^ To ensure comparability reweighting techniques, measurement invariance analysis will be performed. For the reweighting, we will use procedures suggested by Gelman and Carlin.^[32]^ We will collect external information about the distribution of age, place of residence, education level of pregnant women in the population, and adjust our sample to match the proportion in each country. If this is not possible because of the shortage of data, we will use propensity score matching^[33]^ and regression technique to balance the groups’ demographic distributions and make comparisons justifiable. Additionally, to ensure a valid comparison between countries, we will conduct a detailed measurement invariance analysis.^[34]^ Furthermore, we plan to perform regression analyses to explore potential associations between the reported anxiety, depression levels, and medical, sociodemographic, and pandemic related variables (including burdens related to social distancing). Altogether there will be 30 different variables. According to a rule of thumb “N > 104+m”, where N is the number of participants and m is the number of variables, the sample size will allow us to perform all planned analysis.^[35]^ Our main variables (GAD-7 and PHQ-9 scale) are measured by multiple indicators (questions), this opens the possibility to use Confirmatory Factor Analysis (CFA). This technique will allow us to assess the comparability of variables and, if necessary, address the problem of comparability using different latent variable modeling strategies.^[34]^ Principal analysis will be conducted using Structural Equation Modeling Framework which allows us to account not only for comparability problems but as well for measurement error.^[36]^

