Mothers have a strong desire to provide their children with a stable environment, however, the situation of the growing pandemic with strict limitations regarding social contacts and economic instability does not make a secure situation for procreation.^[5]^ Based on the current data, it seems that the severe acute respiratory syndrome coronavirus 2 (SARS-CoV-2) does not cause a severe course of infection in pregnant women as they are usually young and without co-morbidities.^[6]^ It is worth to underline that the COVID-19 pandemic is not only a public health crisis but also a social, demographic and economic one and it has a substantial negative psychosocial effect on everyone, including pregnant women. The resulting anxiety of pregnant women has a negative impact on pregnancy, such as increased risk of preeclampsia, depression, nausea, vomiting and could even cause preterm labor or miscarriage.^[1]^ What is more, maternal anxiety may lead to adverse effects of the newborns, like low birth weight, growth restriction or low APGAR score.^[13,14]^

The primary aim of our study is to compare differences in anxiety and depression scores of pregnant women between countries affected by the COVID-19 pandemic. The secondary aim is to assess demographic, economic, and social aspects affecting maternal anxiety and depression scores among pregnant women worldwide in the time of the COVID-19 pandemic. Finally, we will be able to compare differences in perception of the different aspects of the pandemic (social distancing, restrictions related to delivery) between countries and according to the epidemic status (number of infected patients, number of reported deaths). The comparisons will also be done according to the COVID-19 status of the participants.

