#### Screening questions

2.1.3

The survey has 6 screening questions, of which the first asks if the woman is pregnant or not. It is followed by questions regarding last menstrual period and estimated date of delivery, type of provided care (midwife, doctor, shared, none), and if the pregnancy has been confirmed by a medical professional. This is aimed at decreasing bias created by women claiming to be pregnant to complete the survey.

Demographic and socioeconomic questions ask about place of residence, education, number of people in household, sources of income, marital status, and family/partner support. Pregnancy risk assessment questions include parity, previous mode of delivery, pre-pregnancy chronic diseases, pregnancy-related complications, and infertility treatment. Mental health history questions cover pre-pregnancy and current mental health issues. COVID-19 specific questions cover fear and burden related to COVID-19 pandemic and the restrictions imposed in order to limit the spread of the virus.

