#### Recruitment

2.1.8

Pregnant women will be recruited through social media to complete a web-based survey. Inclusion criteria are the following: declaration of being pregnant, being able to complete the survey in the available languages (English, French, Spanish, Chinese, Polish, German, Russian, Italian, Ukrainian, Czech, Swedish, Albanian, Hebrew, Arabic, and Norwegian), answer the screening questions and provide informed consent for participation.

Exclusion criteria are the following: not providing online informed consent for participation or if the participant does not click on the submit button at the end of the survey, and women who do not answer all the GAD-7 and PHQ-9 scale questions.

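### The balancing variables named for the primary country contrast leave out gestational age, although the dates that give it are asked at screening

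*Protocol article*

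**What the plan says.** The primary aim in the Introduction is to "compare differences in anxiety and depression scores of pregnant women between countries affected by the COVID-19 pandemic".

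Section 2.1.11 (Statistical analysis) sets out how the samples are to be made comparable:

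- The main route collects external data on the "distribution of age, place of residence, education level of pregnant women in the population" and adjusts each country's sample to match.
- If such data are short, the fallback is propensity score matching and a "regression technique to balance the groups’ demographic distributions and make comparisons justifiable".
- A general sentence stands above both: "Reweighting and other techniques will allow adjustment for known or expected discrepancies between sample populations".
- Separately, "we plan to perform regression analyses to explore potential associations between the reported anxiety, depression levels, and medical, sociodemographic" and pandemic-related variables.
- The principal analysis uses structural equation modelling, justified by scale comparability and measurement error. No covariates are listed for it.

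The dates needed for gestational age are collected. After the question on whether the woman is pregnant, section 2.1.3 (Screening questions) states: "It is followed by questions regarding last menstrual period and estimated date of delivery". Section 2.1.8 (Recruitment) makes it an inclusion criterion to "answer the screening questions and provide informed consent for participation". However, section 2.1.7 lets women skip any question they are uncomfortable with and makes only the two scales mandatory.

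Section 2.1.10 (Data collection) describes social media campaigns and posts placed through closed pregnancy groups, with start dates and recruitment rates that may differ by region. Section 3 (Results) calls the method convenience sampling.

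**The concern.** The plan specifies what is to be balanced between countries, and every item named is demographic. Stage of pregnancy is not among them, and nothing in the recruitment scheme equalises it. A campaign that reaches mostly women near term in one country and mostly women in early pregnancy in another would give different gestational mixes. Weighting on age, residence and education need not correct this.

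If GAD-7 or PHQ-9 scores change over pregnancy, part of the observed country difference would be a difference in stage. The article's own topics make a gradient plausible: it asks about restrictions on delivery (Introduction) and discusses worry about infection of the infant around birth (section 4.2). Measurement invariance analysis would not help. It tests whether the scale works alike across countries, not whether the samples have the same make-up. Nor does a larger sample reduce such a bias.

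**Working it through.** **Inputs from the Protocol article, section 2.1.9 (Sample size).** GAD-7 mean 4.75, SD 4.76. PHQ-9 mean 5.2, SD 5.06. Target difference 20%, power 80%, error 0.05, 500 women planned per country.

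**Reproducing the plan's own figures.** Target differences are 0.20 × 4.75 = 0.95 GAD-7 points and 0.20 × 5.2 = 1.04 PHQ-9 points. With n = 2 × [SD × (1.960 + 0.842) / difference]², two-sided:

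- GAD-7: 2 × [4.76 × 2.802 / 0.95]² = 394.1 (stated 394).
- PHQ-9: 2 × [5.06 × 2.802 / 1.04]² = 371.6 (stated 372).

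Both agree, so the sizing corresponds to a two-sided comparison of two means. At 500 per country, power is 88% (GAD-7) and 90% (PHQ-9).

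**Assumptions, not in the documents.** Score gap between early and late pregnancy: 0.5 to 2 points. Difference in late-pregnancy share between two country samples: 10 to 40 percentage points. Both are illustrative.

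**Formulas.** Bias = score gap × difference in share. SE = SD × √(2/500), which is 4.76 × 0.06325 = 0.301 for GAD-7 and 5.06 × 0.06325 = 0.320 for PHQ-9. With no true country difference, the rejection rate is Φ(bias/SE − 1.96) + Φ(−bias/SE − 1.96).

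**GAD-7 results (unweighted test, 500 per country)**

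| Score gap | Share difference | Bias | Bias / 0.95 | False-positive rate |
|---|---|---|---|---|
| 0.5 | 10 points | 0.05 | 5% | 5.3% |
| 1 | 20 points | 0.20 | 21% | 10% |
| 1 | 30 points | 0.30 | 32% | 17% |
| 2 | 20 points | 0.40 | 42% | 26% |
| 2 | 30 points | 0.60 | 63% | 51% |
| 2 | 40 points | 0.80 | 84% | 76% |

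For PHQ-9, the same range gives a bias of 5% to 77% of 1.04 points and rates of 5.3% to 70%. The middle case (1 point, 30 percentage points) gives 15.5%.

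**Effect of weighting.** The planned analysis is weighted or latent, not this simple test. Weighting normally widens the SE. With an assumed design effect of 2, the GAD-7 SE is 0.301 × √2 = 0.426, and biases of 0.20, 0.40 and 0.60 give about 8%, 16% and 29% instead of 10%, 26% and 51%. The bias in points is unchanged.

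**The case against.** The strongest objection is scope. This is a journal article, and covariate lists for a principal model are commonly left to an analysis plan that is not shown. That would settle the matter if the article were silent. It is not: it names a set for the main route and describes the fallback in demographic terms, so following it as written leaves stage of pregnancy unbalanced.

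Four stronger readings are tempting, and the documents do not support them.

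- A reader might infer that countries are balanced *only* on the three named variables. The list identifies the external margins to be collected, the sentence on other techniques is open-ended, and the structural model has no stated covariates. Gestational age is not named, but it is not excluded. Likewise, the regressions on medical variables are described as exploring associations, but the article does not say that they can play no part in the country comparison.
- A reader might infer that gestational age is known for *every* screened woman. The inclusion criterion suggests so, but section 2.1.7 makes only GAD-7 and PHQ-9 mandatory. Completeness of the dates has to be confirmed.
- A reader might infer that any imbalance would arise *purely* from recruitment. When pregnancy is recognised or confirmed could also differ between countries, and the documents do not settle this.
- A reader might take the upper false-positive rates as expected values. They combine large values of both assumptions, and the low end of the range is essentially nominal.

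It is also fair that section 3 admits that representativeness is hard to judge. Its remedy, however, is again an analysis of demographic and socioeconomic factors, which does not reach stage of pregnancy.

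Parity is collected as well, but it may truly differ between countries, so this point does not extend to it.

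**Conclusion.** The point stands in a limited form. Gestational age is missing from the variables named for balancing the primary country contrast, although the dates that determine it are asked at screening. With this sampling scheme the gestational mix may differ between countries, and if scores vary over pregnancy, that would be read as a country difference.

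The size is uncertain: anything from negligible to most of the target difference, with 0.30 points, about a third of the GAD-7 target, as a middle case. This rests on an assumed gradient and an assumed imbalance, for which the documents give no evidence either way. Any gain in precision depends on the same unknown gradient and is not claimed here. The change is worth making because it is cheap and uses data already planned, not because a large bias has been shown.

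**What to change.** In section 2.1.11, or in the analysis plan if one exists, state that gestational age at response, derived from last menstrual period or due date, enters the primary GAD-7 and PHQ-9 country contrasts. Either of two ways will do:

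- as a covariate in the structural or regression model; or
- by standardising all country samples to one common trimester distribution, for example that of the pooled sample.

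Neither needs external population data, unlike adding gestational age to the reweighting margins. Report each contrast with and without the adjustment, so that readers can see how much of a country difference goes with stage of pregnancy. Reconcile sections 2.1.7 and 2.1.8 on whether the screening dates must be answered, and report how many women lack both dates.

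The cost is slightly more analysis work and the possible loss of women with missing dates from the adjusted contrast. No new data are needed, and the sample size does not change.

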A web-based survey can be prone to several types of bias, such as non-response bias, response bias, selection bias, recall bias, and volunteer bias.^[40]^ Although the medium used to propagate the survey is available both in developed and underdeveloped countries, there is a risk that our survey will reach more women of a higher socioeconomic status and from larger agglomerations. To some extent, we could control this bias using historical data collected by conventional methods. In our study, additionally, bias will be accounted for by planning the campaigns for the dissemination of the survey to reach populations in various settings. Response-bias, on the other hand, is a situation when there is a systematic distortion in the way respondents answer the questions. This kind of bias is mainly a problem in surveys that investigate socially unacceptable/embarrassing behavior, that is, alcohol consumption or illegal drug use. Although this is not the case, there is a risk that pregnant women are particularly worried about the COVID-19 pandemic and will be more likely to respond to the advertisement of a survey assessing mental health related to the COVID-19 pandemic. This type of bias is also defined as recall bias, which is often the case in medical surveys where respondents who are prone to a specific sickness, are sick, or are more interested in the disease, are more likely to respond to a survey.^[41]^ For this reason, we will collect background information regarding mental health problems and previous treatments to distinguish such responses. We expect a higher incidence in difficulties with coping with the COVID-19 pandemic in women with a previously diagnosed mental health problem. It has been described that the experience of having the studied condition encourages an ’effort after meaning.’ The participant in such a case has already gone over his/her life history to understand why he/she has become ill. This clearly predisposes to recall bias.^[41]^ Again, this is not the case in our study. Volunteer bias would have occurred if there is a systematic difference between those who volunteer to be part of the study (completed the survey) and the population. In this case, we use a convenience sampling method, which involves sampling participants who are available to be approached at the time of recruitment. Also, we are approaching a specific part of the population – pregnant women. If there were a significant difference between those patients selected for the survey and those who are not, this would result in a sample that is not representative of the population. Convenience sampling is a proven, efficient, cost-effective method of recruitment for a web-based survey.^[42]^ The study aims to assess differences between countries resulting from the COVID19 pandemic. It will be hard to assess if the presented views will reflect the views of the general population of pregnant women in specific countries. This can be accounted for by analyzing the spread of the demographic and socioeconomic factors in the studied populations. The strength of the study is that we are targeting unselected pregnant women.

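### The participant-count rule in section 2.1.11 supports participant-level predictors, but not the planned comparisons by epidemic status, where the effective sample size is the number of countries and dates

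*Protocol article*

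**What the plan says.** Protocol article, section 2.1.11 (Statistical analysis), plans regressions of anxiety and depression on "medical, sociodemographic, and pandemic related variables (including burdens related to social distancing"). It gives the number of predictors: "Altogether there will be 30 different variables". It then applies the rule N > 104 + m, "where N is the number of participants and m is the number of variables, the sample size will allow us to perform all planned analysis". No analysis is excepted.

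The aims in section 1 (Introduction) include comparing how women perceive aspects of the pandemic "between countries and according to the epidemic status (number of infected patients, number of reported deaths").

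Section 2.1.9 (Sample size) sets 500 women per country. Section 2.1.10 (Data collection) does not fix the number of countries; it expresses a hope for at least one per continent. It expects at least six months of collection per language, with staggered starts.

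The bias discussion in section 3 (Results) gives the purpose in causal terms: "The study aims to assess differences between countries resulting from the COVID19 pandemic".

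**The concern.** Numbers of infected patients and deaths describe a population, not a woman. Every respondent in a given country on a given date has the same value. Adding women in that country sharpens its mean outcome but adds no new value of the exposure. A rule that counts women therefore cannot show that the sample is large enough for such a comparison.

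The rule is passed so easily (134 against 500 per country) that it reassures where it does not apply. If the epidemic-status comparisons were then run on individual records without allowing for country, ordinary differences between countries could appear as highly significant associations with cases or deaths. The causal wording in section 3 would encourage readers to credit those differences to the epidemic.

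**Working it through.** **The plan's own figure.** m = 30 (section 2.1.11), so the threshold is 104 + 30 = 134. Section 2.1.9 gives 500 per country, and 500 > 134. The arithmetic is right, and for participant-level predictors the rule is met.

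**Inputs for the epidemic-status comparison**
- n = 500 women per country: section 2.1.9.
- Between-country intraclass correlation (ICC) of the outcome: not in the article. Assumed 0.005 to 0.02, with 0.001 shown as a low case.
- Share r of the predictor's variance that lies between countries: not in the article. r = 1 means counts constant within country; r = 0.5 and r = 0.2 allow for change over the recruitment period.
- Number of countries: not fixed. 6 and 15 used as assumptions.

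**Formulas**
- Design effect DE = 1 + (n − 1) × ICC × r = 1 + 499 × ICC × r.
- True standard error divided by the standard error that treats women as independent = √DE.
- Actual rejection rate of a nominal two-sided 5% test under a true null = 2 × [1 − Φ(1.96/√DE)].

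| ICC | r | DE | √DE | Actual rejection rate |
|---|---|---|---|---|
| 0.001 | 1 | 1.50 | 1.22 | 11% |
| 0.005 | 1 | 3.50 | 1.87 | 29% |
| 0.01 | 1 | 5.99 | 2.45 | 42% |
| 0.02 | 1 | 10.98 | 3.31 | 55% |
| 0.005 | 0.5 | 2.25 | 1.50 | 19% |
| 0.02 | 0.5 | 5.99 | 2.45 | 42% |
| 0.005 | 0.2 | 1.50 | 1.22 | 11% |
| 0.02 | 0.2 | 3.00 | 1.73 | 26% |

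For example, at ICC 0.02 and r = 1: 1 + 499 × 0.02 = 10.98; √10.98 = 3.31; 1.96/3.31 = 0.59; 2 × [1 − Φ(0.59)] ≈ 0.55. The 500 women then carry the information of 500/10.98 ≈ 46 independent ones for this predictor.

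**Check by simulation.** With a null country-level predictor, 500 women per country and 4,000 runs per setting, the participant-level test rejected in 44% (6 countries) and 42% (15 countries) of runs at ICC 0.01, and in 56% for both at ICC 0.02. A test on country means with K − 2 degrees of freedom (K = number of countries) rejected in about 5% throughout.

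**What few countries allow.** With 6 countries, one country-level predictor leaves 6 − 2 = 4 residual degrees of freedom, however many women respond.

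**The case against.** The strongest reply is that the rule directly follows a sentence about regressions on variables the survey collects from each woman, including her own sense of burden and restriction. Nothing in section 2.1.11 places national case or death counts among the 30 variables. On that reading the rule is correctly applied. This stands for those regressions, but the conclusion is worded to cover every planned analysis, and the epidemic-status comparison is one of them.

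Three stronger readings are tempting, and the article does not support them.
- *That the analysis will use standard errors that are too small.* The article names structural equation modelling in R and Mplus and does not say how country enters or which standard errors apply. Such detail may sit in a fuller plan. The inflation is conditional; the over-broad sufficiency statement is not.
- *That the paired means in section 2.1.9 show how far countries differed before the pandemic.* That section does not say the members of each pair come from different countries, and the lower PHQ-9 mean is for ages 30–39. No between-country ICC can be drawn from them.
- *That GAD-7 and PHQ-9 are to be regressed on cases and deaths.* The Introduction ties epidemic status to perceptions. The point holds for any outcome compared by these counts, but the article does not explicitly plan that regression for the two scores.

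It is also fair that counts will change within a country over six months or more, so r = 1 is an upper case. This reduces the error, as the table shows, but removes it only if almost none of the predictor's variance lies between countries.

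**Conclusion.** The concern holds in limited form. Section 2.1.11 claims sufficiency for all analyses from a count of participants, and that is wrong for the comparisons by numbers infected and deaths. The other safeguards described there do not repair it: reweighting and matching balance demographics, invariance analysis addresses comparability of the scales, and the structural equation framework is offered for comparability and measurement error.

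Under independent-participant analysis, the standard errors would be about 1.9 to 3.3 times too small and the false-positive rate about 29% to 55%. This rests on three assumptions: ICC 0.005 to 0.02, 500 women per country, and counts constant within country. At ICC 0.001 the factor is only 1.2.

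Participant-level predictors are unaffected. So is the primary aim, which compares countries as fixed groups. The point is worth correcting before analysis, but it does not undermine the main comparison.

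**What to change.** - In section 2.1.11, limit the 104 + m statement to participant-level predictors. State that the sample size for epidemic-status analyses is the number of countries (and dates), and that 500 women per country does not settle it.
- Analyse epidemic counts with country-clustered inference: a two-level model of women within countries, or a country-level test with small-sample degrees of freedom. With few countries the latter is safer, because a random-intercept variance is then poorly estimated.
- Enter date-specific counts split into a within-country and a between-country part, and label between-country associations as descriptive.
- In section 3, replace the causal phrase with wording that refers to differences between countries during the pandemic.

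The cost is a change of wording and of model; the software already named can be kept, though date-specific national counts and each woman's survey date are needed. The price is wider intervals for the epidemic variables and, if few countries enrol, little inference about them at all.
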